
### Standard care

All the participants in both groups will attend standard antenatal care at their trial centre and will be provided with regular treatments if diagnosed with GDM. The control group will fill in five 3-day food records at designated gestational week periods (13–16 w, 17–20 w, 21–24 w, 27–30 w, 32–34 w) but will not be scheduled to see a study-specific dietician as part of the study. However, the control group participants will be allowed to visit nutritionists themselves for usual antenatal healthy diet advice in accordance with local health care provisions.

### Withdrawal of participants

The participants will be informed clearly by investigators at enrolment that they may withdraw from the study at any period for any reason without penalty. Written consent will be obtained if the participant agrees to undergo continued follow-up for associated clinical outcomes after withdrawal.

### Participant timeline

The time schedule of recruitment, intervention, and outcome assessments is presented in Table 1 (see Additional file 2). All pregnant women will take a blood test assessing fasting glucose, HbA1c, and blood triglyceride levels in the first trimester. The number of foetuses will be determined by ultrasound in early pregnancy. After the required data are obtained, the recruiting staff will screen every single pregnant woman at antenatal clinics using the prediction model to determine their eligibility for the study and initiate recruitment as specified previously. Written informed consent, baseline information, and baseline blood pressure plus anthropometric measurements (body weight, height) will be obtained at recruitment. Fasting body weight measured in light clothing without shoes as well as blood pressure will be followed up at 1-month intervals during antenatal visits. The first 3-day food record will be distributed at first contact. Women in the intervention group will receive 3 nutritional consultations that will be paired with 3-day food records at 13–16, 17–20, and 21–24 gestational weeks before the OGTT and submit 2 more diaries after (27–30 w, 32–34 w). The participants in the control group will return their diaries directly to research staff 5 times throughout gestation (13–16 w, 17–20 w, 21–24 w, 27–30 w, 32–34 w). All the participants in both arms will be required to take a 75 g OGTT at 24–28 gestational weeks, the results of which will be the primary end point.

**Table 1 Tab1:**
[figure not shown]
Data collection schedule

### Proposed outcome measurement

#### Primary outcome

GDM diagnosis via a 75 g OGTT at 24–28 gestational weeks will be the primary end point, which is defined as meeting or exceeding any one of the following plasma glucose values in the one-step screening: fasting plasma glucose ≥5.1 mmol/L; 1-h value ≥10.0 mmol/L; and 2-h value ≥8.5 mmol/L (adapted from the IADPSG and the ADA [2, 3]).

#### Secondary outcomes [36]

*Maternal-* GWG, hypertensive disorders of pregnancy (gestational hypertension, preeclampsia), placental abruption, preterm/prelabor/ rupture of membranes (P/PROM), mode of birth (vaginal delivery/operational vaginal delivery/elective or emergency caesarean section), blood loss during birth, postpartum haemorrhage, adherence to the intervention, requirement for insulin therapy, total daily insulin dose, and maternal mortality will be assessed. GWG will be recorded to the nearest 0.1 kg as the difference between self-reported pre-pregnancy weight and the last measurement of weight prior to delivery in the hospital [37]. Gestational hypertension will be defined as de novo hypertension (≥ 140/90 mmHg) on two occasions at least 4 h apart after 20 gestational weeks without proteinuria or other biochemical, systematic, or severe features in a woman who was normotensive preconception. Preeclampsia will be diagnosed when gestational hypertension is accompanied by any of the following presentations: new-onset proteinuria (≥ 0.3 g/24 h), thrombocytopenia (PLT ≤ 100,000 × 10^9/L), renal insufficiency, impaired liver function or pulmonary oedema [38]. Maternal biochemical outcomes include the OGTT results (fasting, 1-h and 2-h glucose values), fasting plasma insulin level, and insulin resistance calculated by homeostatic model assessment 2 (HOMA2-IR) at 24–28 gestational weeks and average fasting glucose level, HbA1c level, haemoglobin concentration, and lipid profile [low-density lipoprotein (LDL), high-density lipoprotein (HDL), triglycerides, total cholesterol] at the 3rd trimester.

*Neonatal-* Infant sex; gestational age at birth (based on estimated date of delivery); Apgar score; birth length; birth weight assessed for macrosomia (≥ 4000 g), low birth weight (< 2500 g), large for gestational age (LGA), and small for gestational age (SGA); preterm birth (PTB, < 37 weeks); shoulder dystocia; bone fracture; bronchial plexus injury; neonatal hypoglycaemia; neonatal respiratory distress; jaundice for which treatment is warranted; neonatal intensive care unit (NICU) admission; congenital anomalies; livebirth; miscarriage (< 20 weeks); still birth (≥ 20 weeks); and neonatal death (within the first 28 days after delivery) will be assessed. LGA and SGA will be defined as a birth weight above the 90th or below the 10th percentiles of newborns of the same gestational age and sex, respectively, in accordance with the INTERGROWTH-21st growth standards published in 2014 [39]. Neonatal hypoglycaemia refers to venous glucose levels lower than 2.6 mmol/L within the first 48 h after birth.

*Dietary-* Daily average energy intake, macronutrient intake (proteins, fats, carbohydrates), vitamin intake (vitamin A, vitamin D, vitamin E, vitamin C, vitamin B1, vitamin B2, niacin, and folic acid), mineral intake (calcium, phosphorus, iron, and zinc), and dietary fibre intake (g) will be assessed.

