#### Data collection

At the time of enrolment, data on demographic characteristics, socioeconomic status, smoking habit, alcohol consumption, self-reported morbidity, menstrual and obstetric history, first-degree family history of diabetes, hypertension, stroke, hyperlipidaemia and obesity will be collected using a baseline questionnaire. Gestational weeks, height, weight and resting blood pressure will be measured and recorded by research staff at the time of enrolment and at each follow-up visit during prenatal care, as shown in Table 1. BMI is equal to the weight in kilograms divided by height in metres squared (kg/m^2^). Maternal age; pre-pregnancy weight and BMI; parity; prior GDM; family history of diabetes; number of foetuses; prenatal diagnoses; laboratory results of fasting glucose level, HbA1c level, and triglycerides at the 1st trimester; OGTT results of fasting, 1-h and 2-h glucose values and fasting plasma insulin at 24–28 weeks gestation; and average fasting glucose level, HbA1c level, haemoglobin concentration, and lipid profile at the 3rd trimester during 32–34 gestational weeks will be collected from the outpatient electronic medical record (EMR). Data on maternal and neonatal secondary outcomes stated above will be obtained from inpatient EMRs and will be confirmed by research clinicians. In the intervention arm, poor adherence to the intervention will be considered as failure to complete 3 nutritional consultations or at least 4 sets of qualified 3-day food records at the appropriate times. If food quantification information is missing from a 3-day food record, it will be recognised as invalid. The criteria for diet diaries will be equally applicable to the control arm. Dietary statistics will be processed and calculated automatically by NutriStar Software based on 3-day food records provided by the participants.

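### The platelet cut-off in the preeclampsia definition pairs a number and a unit that do not fit together, so as printed any real platelet count meets it

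*Protocol article*

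**What the plan says.** The Secondary outcomes section of the protocol article lists, among the maternal outcomes, "hypertensive disorders of pregnancy (gestational hypertension, preeclampsia" as two named components. Gestational hypertension is new hypertension after 20 weeks, found on two occasions at least 4 h apart, "without proteinuria or other biochemical, systematic, or severe features".

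For the other component the rule is: "Preeclampsia will be diagnosed when gestational hypertension is accompanied by any of the following presentations". The list that follows has five entries. Two carry a numerical cut-off: proteinuria, and the platelet criterion, printed as "thrombocytopenia (PLT ≤ 100,000 × 10^9/L". Renal insufficiency, impaired liver function and pulmonary oedema are named without a number. The definition is referenced to source 38. No other part of the article gives a platelet cut-off.

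On where the data come from, the Data collection section says that maternal and neonatal secondary outcomes "will be obtained from inpatient EMRs and will be confirmed by research clinicians".

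**The concern.** The figure 100,000 belongs with a count per microlitre. The unit × 10^9/L belongs with a figure a thousand times smaller. The printed criterion joins the two, so a factor of 1,000 appears to be counted twice. The result is an upper limit so high that it does not separate low counts from normal ones.

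This matters more than a slip in background text would, because the figure is a decision threshold in an outcome definition and the criteria are joined by an any-of rule. One criterion that is always true settles the classification whatever the others show. Gestational hypertension is in turn defined by the absence of biochemical features, so what the preeclampsia category gains, the gestational hypertension category loses. At stake are the separate counts of these two components, and any comparison of them between the arms.

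**Working it through.** **Inputs from the document** (Secondary outcomes section)
- Printed cut-off: at or below 100,000 × 10^9/L.
- Combination rule: gestational hypertension plus any one listed presentation is preeclampsia.
- Gestational hypertension requires that no such feature is present.

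**Step 1: the printed figure in plain units.**
- Per litre: 100,000 × 10^9 = 10^5 × 10^9 = 1 × 10^14.
- Per microlitre: 1 × 10^14 ÷ 10^6 = 1 × 10^8, that is 100 million.

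**Step 2: the same number with a per-microlitre unit.**
- 100,000 per microlitre × 10^6 microlitres per litre = 1 × 10^11 per litre = 100 × 10^9/L.
- Ratio of the printed figure to this one: 1 × 10^14 ÷ 1 × 10^11 = 1,000.

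**Step 3: can any real count fail the criterion?** The document gives no platelet range, so I assumed one from 20 to 5,000 × 10^9/L, deliberately far wider than usual. Every value in it satisfies the printed criterion:

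| Assumed count (× 10^9/L) | Printed cut-off ÷ count | Meets the criterion as printed |
|---|---|---|
| 20 | 5,000 | yes |
| 100 | 1,000 | yes |
| 150 | 667 | yes |
| 450 | 222 | yes |
| 5,000 | 20 | yes |

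A second check uses volume. With an assumed mean platelet volume of 7 to 12 fL (1 fL = 10^-15 L), platelets at the printed cut-off would occupy 1 × 10^14 × 7 × 10^-15 = 0.7 L to 1 × 10^14 × 12 × 10^-15 = 1.2 L of each litre of blood. No real sample reaches that, so the criterion excludes nobody.

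**Step 4: what the any-of rule does with it.** Take a woman who meets the blood-pressure part of the gestational hypertension definition and has a platelet count on record. The platelet criterion is true whatever the count, so she is classified as preeclampsia. This applies to all such women, whatever the event rate. Gestational hypertension is left empty, apart from any woman with no count on record.

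**Step 5: what does not move.** The shift is between two components of one outcome. A woman counted under hypertensive disorders of pregnancy is still counted there. The primary outcome rests on glucose values from the OGTT, and the sample size on GDM incidence, so neither is touched.

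**The case against.** The strongest reply is that nobody would use the figure as printed. The criterion is named thrombocytopenia, and a limit that every woman is below cannot describe a low count, so a clinician sees at once that two unit conventions were merged. The protocol also keeps gestational hypertension as a category of its own, and a reading that empties it is plainly not intended. The outcomes are confirmed by research clinicians, who would not accept a normal count as thrombocytopenia. This stands, and it makes actual misclassification unlikely.

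It also rules out a stronger reading. A reader might infer that the two outcomes are computed from laboratory values in the electronic record, so that all gestational hypertension in this trial will be reported as preeclampsia. The document does not support that. It says that the outcomes are obtained from inpatient records and confirmed, which fits abstraction of hospital diagnoses at least as well as a programmed rule. Platelet count is not among the laboratory results listed under Data collection, nor among the maternal biochemical outcomes. Complete reclassification would need platelet values to be extracted, the rule to be coded literally, and clinician confirmation to fail every time. The document establishes none of these.

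The reply does not make the definition correct. Confirmation across three hospitals needs a written criterion that can be applied, and this one cannot. Nor is this a matter of detail left to a fuller document: the article states a value, and the value does not work.

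**Conclusion.** The point holds as an error in the wording of a secondary-outcome definition. The printed platelet cut-off is 1,000 times the value obtained by reading the same number per microlitre, and it is met by any real count. Applied literally, it would move every gestational hypertension case with a recorded platelet count into preeclampsia. The combined hypertensive-disorders outcome, the primary outcome and the sample size are unaffected.

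The unit arithmetic rests on the document alone. That no real count exceeds the cut-off rests on the assumed platelet range and volume, both generous. The likely practical harm is small, for the reasons accepted above. The document proves that number and unit disagree, but not which of the two was mis-set. That has to be settled from the cited source.

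**What to change.** Reconcile the number and unit of the platelet cut-off with the definition cited as reference 38, so that they express one consistent value. For orientation only, 100,000 per microlitre and 100 × 10^9/L are the same quantity. Give the reconciled value to the research clinicians who confirm the outcome at the three centres, and use it in any coding of the outcome. If a rule has already been coded or preeclampsia cases already confirmed, check which figure was used. The cost is one figure in the outcome definition and, where such work exists, a short check. Design, sample size and analysis stay as they are.

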#### Data collection

At the time of enrolment, data on demographic characteristics, socioeconomic status, smoking habit, alcohol consumption, self-reported morbidity, menstrual and obstetric history, first-degree family history of diabetes, hypertension, stroke, hyperlipidaemia and obesity will be collected using a baseline questionnaire. Gestational weeks, height, weight and resting blood pressure will be measured and recorded by research staff at the time of enrolment and at each follow-up visit during prenatal care, as shown in Table 1. BMI is equal to the weight in kilograms divided by height in metres squared (kg/m^2^). Maternal age; pre-pregnancy weight and BMI; parity; prior GDM; family history of diabetes; number of foetuses; prenatal diagnoses; laboratory results of fasting glucose level, HbA1c level, and triglycerides at the 1st trimester; OGTT results of fasting, 1-h and 2-h glucose values and fasting plasma insulin at 24–28 weeks gestation; and average fasting glucose level, HbA1c level, haemoglobin concentration, and lipid profile at the 3rd trimester during 32–34 gestational weeks will be collected from the outpatient electronic medical record (EMR). Data on maternal and neonatal secondary outcomes stated above will be obtained from inpatient EMRs and will be confirmed by research clinicians. In the intervention arm, poor adherence to the intervention will be considered as failure to complete 3 nutritional consultations or at least 4 sets of qualified 3-day food records at the appropriate times. If food quantification information is missing from a 3-day food record, it will be recognised as invalid. The criteria for diet diaries will be equally applicable to the control arm. Dietary statistics will be processed and calculated automatically by NutriStar Software based on 3-day food records provided by the participants.

### Statistical methods

#### Sample size calculation

The incidence of GDM among high-risk women determined by the prediction model is approximately 30% in accordance with the IADPSG criteria on the basis of our unpublished data. Assuming a clinically important 30% reduction in GDM incidence in the intervention arm and allowing for 10% dropout, the calculated sample size of 464 subjects (232 per group) would provide 80% power with a two-tailed alpha error of 0.05. Thus, we aimed to recruit 500 women in total (250 per group), anticipating that at least 450 participants would complete the trial.

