**Methods/design:**

A multicentre randomised controlled trial was designed to assess the efficacy of an individualised nutritional intervention for the prevention of GDM in a high-risk population screened by a novel prediction model in the first trimester. Pregnant women evaluated to be at high risk for GDM by the prediction model at less than 14 gestational weeks will be included. Women with pre-existing chronic diseases, including pregestational diabetes, or who are currently prescribed medicines that affect glucose values will be excluded. Allocation to intervention/control at a ratio of 1:1 will be conducted by a computerized randomisation system. The intervention group will complete 3-day food records and receive 3 individualised nutritional consultations with professional dieticians before the oral glucose tolerance test. The primary intention of the intervention is to promote a long-term healthy dietary pattern and prevent excessive gestational weight gain throughout pregnancy. The control group will complete 3-day food records at designated gestational weeks and receive standard antenatal care according to local health care provisions. The primary outcome is the incidence of GDM according to the criteria of the International Association of Diabetes and Pregnancy Study Group (IADPSG). A sample of 464 participants will provide 80% power to detect a 30% reduction in GDM incidence (α = 0.05 two tailed, 10% dropout). A total of 500 participants will be recruited.

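### The stated 464 women (232 per group) give about 56–61% power, not 80%, for a 30% reduction from a 30% GDM incidence; the planned 450 completers give about 59%

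*Protocol article*

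**What the plan says.** The Sample size calculation section of the protocol article states each input. On the baseline: "The incidence of GDM among high-risk women determined by the prediction model is approximately 30% in accordance with the IADPSG criteria", attributed to the group's unpublished data. On the effect and losses: "Assuming a clinically important 30% reduction in GDM incidence in the intervention arm and allowing for 10% dropout". On the result: "the calculated sample size of 464 subjects (232 per group) would provide 80% power with a two-tailed alpha error of 0.05". The section then raises recruitment to 500 (250 per group) and expects at least 450 women to complete.

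The abstract (Methods/design) carries the same claim: "A sample of 464 participants will provide 80% power to detect a 30% reduction in GDM incidence (α = 0.05 two tailed, 10% dropout".

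Other sections settle the rest of the calculation. Allocation is 1:1 (Recruitment and randomisation), categorical data are compared by the Pearson chi-square test (Statistical analysis), and no interim analysis is planned (Data monitoring and auditing), so alpha is not divided.

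**The concern.** The absolute difference implied by the inputs is 9 percentage points (30% to 21%). A two-arm comparison of proportions near 25% normally needs well over 300 women per arm to detect a difference of that size with 80% power at two-sided 0.05. A figure of 232 per arm that already includes dropout is far too small.

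This is the power statement for the only primary endpoint, and it stands in the abstract. The Background presents the evidence as conflicting and argues for adequately powered research. It cites a 269-woman trial in Finland with GDM in 13.9% versus 21.6%, a relative reduction of 1 − 13.9/21.6 = 36%, and a UK trial with 25.0% versus 26.0%, a reduction of about 4%. A non-significant result read alongside a claimed 80% power invites the conclusion that a 30% reduction has been ruled out. If the true power is about 59%, that conclusion is not supported.

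**Working it through.** **Inputs** (all from the protocol article)

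- Control incidence p1 = 0.30 (Sample size calculation).
- 30% relative reduction, so p2 = 0.70 × 0.30 = 0.21 and the difference is 0.09 (Sample size calculation; abstract).
- Two-sided alpha 0.05, z = 1.96; power 80%, z = 0.8416 (same places).
- Dropout 10%; 1:1 allocation; no interim analysis.

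The text does not say whether the reduction is relative. Read as 30 percentage points it would mean no GDM at all in the intervention arm and would need only about 22 women per group, so relative is the only workable reading.

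**Step 1: try to reproduce 232 per group**

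Unpooled variance:

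n = (1.96 + 0.8416)² × (0.30 × 0.70 + 0.21 × 0.79) / 0.09² = 7.849 × 0.3759 / 0.0081 = 364.2, so 365 per group.

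Pooled variance under the null, with mean proportion 0.255:

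n = [1.96 × √(2 × 0.255 × 0.745) + 0.8416 × √0.3759]² / 0.09² = (1.2081 + 0.5160)² / 0.0081 = 367.0 per group.

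Other standard versions at two-sided 0.05 give 366 (arcsine), 377 (log risk ratio) and 389 (pooled with continuity correction). One-sided 0.05 (pooled) still needs 289 per group before dropout. None gives 232.

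After dropout: 365/0.9 = 405.6 and 367/0.9 = 407.8, so 406–408 per group, or about 810–816 recruited. The stated 464 is 464/816 = 57% of the pooled figure.

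**Step 2: power at the planned sizes**

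Power = Φ{[0.09 × √n − 1.2081] / 0.6131}, where 0.6131 = √0.3759. For n = 225: (0.09 × 15 − 1.2081)/0.6131 = 0.231, and Φ(0.231) = 0.59. The last column is an exact enumeration of the Pearson chi-square test.

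| Women per group | What it represents | Normal approximation | Exact |
|---|---|---|---|
| 209 | 464 less 10% (208.8 per group) | 56.0% | 56.2% |
| 225 | 450 completers | 59.2% | 59.5% |
| 232 | 464, no loss | 60.5% | 60.7% |
| 250 | 500, no loss | 63.7% | 64.0% |

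**Step 3: what the design can detect with 80% power**

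Solving the pooled formula for p2 with p1 = 0.30:

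- 225 per group: p2 = 0.187, a relative reduction of 37.7%.
- 209 per group: p2 = 0.183, a relative reduction of 39.0%.

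**Step 4: sensitivity to the baseline**

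With a 30% relative reduction and 225 per group, power is 49% at a baseline of 25%, 59% at 30%, 68% at 35% and 77% at 40%. Reaching 80% needs a baseline of about 42% (about 44% at 209 per group).

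**Step 5: where 232 might have come from**

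The article gives no formula, so these are assumptions about origin and the finding does not rest on them.

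- Alpha entered as two-sided 0.20 (z = 1.2816), unpooled: (1.2816 + 0.8416)² × 0.3759/0.0081 = 209.2; 209.2/0.9 = 232.4.
- A 40% reduction (30% to 18%), unpooled with continuity correction: 211.25 × 1.1 = 232.4.

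Each contradicts a stated input.

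**The case against.** The strongest reply is that the baseline is only approximate and rests on unpublished data, so 59% holds only if control incidence is exactly 30%. That is fair as a condition, and any restated power should carry it. It does not rescue the claim: a baseline of 35% gives 68%, and the roughly 42% needed for 80% cannot be called a rounding of 30%. A baseline below 30% makes matters worse.

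The Statistical analysis section also plans analyses adjusted for baseline values, which could change power somewhat. The sample size section claims no such gain and gives no figure for one, so the stated 80% cannot rest on it.

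Two further points stand in part. The same section already plans risk ratios and risk differences with 95% confidence intervals, so what is missing is only a statement of how a non-significant result will be read; that such a result would be over-read is a judgement about readers, not something the protocol says. And whether to keep the sample size or the 30% target is for the investigators to decide, so a larger trial belongs among the options.

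An unseen analysis plan or full protocol could not settle the matter, because the article itself ties these inputs to this number.

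**Conclusion.** The concern holds. On the protocol's own inputs, 80% power requires 365–367 evaluable women per group, not 232 per group including dropout. The stated 464 gives 56% power after 10% dropout and about 61% with none. The 450 expected completers give about 59%, and the increase to 500 does not repair the shortfall. A true 30% reduction would be missed about 41% of the time, not 20%.

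This assumes a relative reduction, a control incidence of 30%, and an unadjusted two-sided comparison of two proportions. The choice of variance formula moves the required number only from 365 to 389 per group before dropout. The conclusion does not depend on how the error arose.

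**What to change.** Correct the sentence in the Sample size calculation section and the matching one in the abstract, along these lines: *With 500 women recruited and 450 completing, and assuming a control incidence of 30%, the trial has about 59% power (two-sided alpha 0.05) for a 30% relative reduction (30% to 21%) and 80% power for a 38% relative reduction (30% to 18.7%).* A short note that power runs from about 49% to 68% for baselines of 25% to 35% would show the dependence on the baseline.

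Add one sentence committing to interpret the primary result by its confidence interval, and not to describe a non-significant result as evidence against a 30% reduction.

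If the calculation used a different effect or alpha, such as a 40% reduction, state it and reconcile the text with it. If 80% power for a 30% reduction is to be kept, the alternative is about 816 women recruited.

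The recommended correction needs no extra participants and no change to design or conduct. Its cost is a few sentences and a less favourable stated power; enlarging the trial would cost about 816 − 500 = 316 more women.
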